**Methods:**

This pilot randomized controlled trial will assess the feasibility of implementing the IPS model for adults with SMI in Jalisco, Mexico. We will recruit 120 participants who are actively seeking employment and randomly assign them to either the IPS intervention or a control group receiving standard employment services. The intervention includes tailored support from trained IPS Employment Specialists in resume building, interview preparation, job search, and follow-up after job placement. Primary feasibility outcomes include recruitment and retention rates, participant acceptance, implementation fidelity, and identification of contextual barriers and facilitators. Secondary outcomes will explore employment status at 12 months, financial well-being, and health-related outcomes.

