#### Progression criteria for a future definitive trial

Progression to a future definitive trial will be guided by a pre-specified traffic-light framework across four feasibility domains: recruitment, retention, IPS fidelity, and acceptability. Transparent “red–amber–green” thresholds will guide decisions regarding continuation, amendment, or discontinuation of a future trial (Table 4).Recruitment will be assessed as the proportion of achieved versus planned recruitment at matched timepoints during the recruitment period. Recruitment performance will be classified as green if ≥ 85% of the planned recruitment target is achieved, amber if 70–84% is achieved, and red if < 70% is achieved.Retention will be evaluated at the primary follow-up timepoint (12 months). Retention will be classified as green if ≥ 77% of participants are retained, consistent with the retention benchmark anticipated in the study protocol, amber if retention is 60–76%, and red if retention is < 60%.IPS fidelity will be assessed using the IPS-25 Fidelity Scale, a validated instrument widely used to evaluate adherence to the IPS model. Fidelity will be classified as green if the program achieves a score ≥ 100 (indicating good fidelity), amber if scores fall between 74 and 99 (fair fidelity requiring improvement), and red if scores are ≤ 73 (not IPS fidelity).Acceptability will be evaluated using a combination of quantitative participant ratings and qualitative interview data. Quantitative acceptability ratings will be summarized descriptively, and qualitative findings will be interpreted within established implementation science frameworks. Acceptability will be classified as green when quantitative ratings indicate generally favorable perceptions and qualitative data reveal no major barriers to participation; amber when mixed perceptions or remediable barriers are identified; and red when qualitative evidence identifies substantial concerns or barriers that would likely preclude successful implementation of a definitive trial.

**Table 4 Tab4:** Pre-specified progression criteria for feasibility outcomes

Feasibility domain	Green (proceed)	Amber (amend)	Red (stop/reconsider)
Recruitment	≥ 85% of target recruitment achieved	70–84% achieved	< 70% achieved
Retention (12 months)	≥ 77% retained	60–76% retained	< 60% retained
IPS fidelity (IPS-25 scale)	≥ 100 (good fidelity)	74–99 (fair fidelity)	≤ 73 (not IPS fidelity)

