#### Sample size

The study will include a convenience sample of 120 participants, with 60 allocated to each group. As this is a pilot feasibility trial, no formal power calculation was conducted. Instead, the sample size was determined based on feasibility considerations, alignment with previous IPS pilot studies in similar contexts [17, 18], and the need to generate stable estimates of recruitment, retention, and preliminary variability in outcomes.

This approach is consistent with current methodological guidance for feasibility studies, which emphasizes that sample sizes should be justified according to their ability to assess feasibility parameters rather than to detect statistically significant effects. Feasibility trials aim to inform the design and sample size of a future definitive randomized controlled trial rather than to conduct hypothesis testing or achieve statistical power. The selected sample size is therefore appropriate to evaluate the acceptability, feasibility, and preliminary implementation of the adapted IPS model in this setting and to inform the parameters required for a fully powered RCT [19].

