#### Recruitment

The study will implement several recruitment strategies over a 12-month period to enroll 120 participants with 1 year of planned follow-up. Clinicians at the Center for Comprehensive Care in Long-Stay Mental Health will identify potential participants during routine care and refer them to informational sessions offered by the psychosocial rehabilitation service. Promotional materials (e.g., posters and flyers) will be placed in waiting areas and hallways to raise awareness.

Research staff will conduct informational sessions and provide individual outreach to support ongoing recruitment. Individuals who attend a session and express interest in employment will be screened for eligibility, complete the informed consent process, undergo randomization to either usual care or the adapted IPS intervention, and complete the baseline assessment.

Recruitment projections are based on previous IPS trials that achieved consistent enrollment through sustained collaboration with clinical teams and use of incremental recruitment targets [20]. Participant feedback and service utilization data will be used to refine recruitment procedures throughout the study.

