### Assignment of interventions: allocation

#### Sequence generation

This study follows a randomized, controlled, outcome-assessor-blinded, parallel-group design. To ensure balance between the intervention (IPS) and control (Usual Care) groups, permuted block randomization with a block size of four will be used. Accounting for an expected 25% attrition rate, the study will recruit 160 participants, arranged in 40 blocks, to meet the target sample size of 120 participants.

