#### Plans to promote participant retention and complete follow-up

This study enrolls clients who are already receiving services at the participating site and have established relationships with clinical providers. Combined with pre-recruitment informational sessions and the ongoing engagement of clinicians and research staff, this approach has yielded high retention rates—exceeding 90% at 1- and 2-year follow-up—in similar studies. However, given the limited precedent for IPS implementation in Mexico, we account for a more conservative retention estimate. For example, the Supported Employment Demonstration reported a 77% 1-year IPS participation rate [28]. Accordingly, we anticipate a retention rate of approximately 77%, and this figure informed our sample size and recruitment planning to ensure adequate follow-up data.

To maximize retention and minimize attrition, we will implement several strategies: clearly explaining study requirements prior to enrollment; conducting assertive outreach; collecting updated locator information at each contact point; maintaining regular communication; and providing compensation for each completed interview. Participants will remain eligible for follow-up assessments regardless of their level of engagement with IPS services. Prior studies suggest that participants often stay engaged due to a desire to share their experiences and contribute to the improvement of mental health services.

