### Statistical methods for primary and secondary outcomes

Primary feasibility outcomes will be analyzed descriptively. Recruitment and retention will be summarized as proportions with 95% confidence intervals. Fidelity scores will be summarized using total and domain scores at each assessment point. Acceptability findings will be integrated descriptively with qualitative data. Quantitative analyses will follow an intent-to-treat approach. Employment, financial well-being, and health-related outcomes will be analyzed using linear generalized mixed models, accounting for clustering at the site level. Effect sizes will be reported with 95% confidence intervals to assess the direction and magnitude of potential impacts. Preliminary analyses will examine data distributions and apply transformations where necessary. Baseline characteristics will be summarized descriptively by randomized group to describe the study sample. No statistical tests will be conducted to compare baseline variables between groups, as any differences are expected to occur by chance due to randomization. Where appropriate, pre-specified prognostic covariates may be included in adjusted models to improve precision of effect estimates. Secondary analyses will include employment trajectories, non-vocational outcomes, and analyses based on level of exposure to the intervention. Longitudinal data will be analyzed using mixed-effects models. Time-to-event outcomes will be evaluated using Kaplan–Meier curves and Cox proportional hazards models.Qualitative data will be analyzed using a flexible coding approach. An initial multilevel codebook (systemic, organizational, provider, participant) will guide the deductive phase of coding, followed by the identification of inductive codes emerging from transcript review. Coding will be conducted by multiple team members who will meet regularly to refine the codebook and resolve discrepancies through discussion and consensus. Once coding is complete, excerpts will be organized into a structured matrix to compare perspectives across stakeholder groups and to identify salient barriers, facilitators, and implementation needs. This analytic strategy is consistent with methods used in the Preparation Phase and follows established approaches in implementation science.

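### The number to be randomised is 120 in most sections and 160 under Sequence generation, and the recruitment progression criterion does not say which is its target, so some enrolment totals rate green or red

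*Protocol article*

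**What the plan says.** The Abstract states: "We will recruit 120 participants who are actively seeking employment and randomly assign them". Trial design gives the pilot's size as N = 120. Under Sample size: "The study will include a convenience sample of 120 participants, with 60 allocated to each group". Recruitment describes strategies "over a 12-month period to enroll 120 participants with 1 year of planned follow-up".

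Sequence generation differs: "Accounting for an expected 25% attrition rate, the study will recruit 160 participants, arranged in 40 blocks", with 120 as the target sample size to be met after that attrition. The block size is four.

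Under Progression criteria for a future definitive trial: "Recruitment will be assessed as the proportion of achieved versus planned recruitment at matched timepoints during the recruitment period". Green is 85% or more of target, amber 70–84%, red below 70%. Neither that text nor Table 4 gives the planned number. Retention at 12 months is green at 77% or more, amber at 60–76% and red below 60%.

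The section on promoting retention says: "we anticipate a retention rate of approximately 77%, and this figure informed our sample size and recruitment planning".

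**The concern.** Two statements about the same quantity cannot both hold. If 60 people are allocated to each group, 120 are randomised and fewer than 120 will have 12-month data. If 160 are randomised so that 120 remain, 80 are allocated to each group and 120 is the number retained. Reading 120 as completers everywhere does not reconcile the text, because the Abstract, Sample size and Recruitment sections attach it to recruiting, allocating and enrolling.

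The conflict reaches a result that the trial will report. Recruitment is a primary feasibility outcome and one of four progression domains, scored as a ratio whose denominator is the disputed number. If nothing is fixed in advance, the denominator could be chosen once the enrolment total is known.

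Retention has a related problem. Attrition is 25% in one section and about 23% in another, and the two values fall on opposite sides of the green cut-off.

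**Working it through.** **Inputs.** Target sample size 120, attrition 25%, block size 4 (Sequence generation). Number allocated 120, 60 per group (Sample size). Anticipated retention about 77% (retention section). Rating bands (Progression criteria and Table 4).

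**1. Reproducing the plan's figure.** Number to recruit = target/(1 − attrition) = 120/(1 − 0.25) = 160. Blocks = 160/4 = 40. Both agree with Sequence generation, so there is no arithmetic error there.

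**2. The two readings of 120.**

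| | 120 is the number randomised | 120 is the number retained |
|---|---|---|
| Randomised | 120 | 160 |
| Blocks of four | 30 | 40 |
| Per arm | 60 | 80 |
| Expected at 12 months, 75% retained | 90 | 120 |
| Expected at 12 months, 77% retained | 92.4 | 123.2 |

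**3. Recruitment cut-offs.** Green cut = 0.85 × target; red lies below 0.70 × target.
- Target 120: green from 0.85 × 120 = 102; red below 0.70 × 120 = 84.
- Target 160: green from 0.85 × 160 = 136; red below 0.70 × 160 = 112.

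| Total enrolled | Rated on 120 | Rated on 160 |
|---|---|---|
| 83 or fewer | red | red |
| 84–101 | amber | red |
| 102–111 | green (85.0–92.5%) | red (63.8–69.4%) |
| 112–135 | green | amber |
| 136 or more | green | green |

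Enrolling exactly 120 is 120/120 = 100% (green) or 120/160 = 75% (amber). Rounding to whole percentages does not move these cut-offs: 101/120 = 84.2% and 135/160 = 84.4% both round to 84%, and 83/120 = 69.2% and 111/160 = 69.4% both round to 69%.

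Scoring at matched timepoints does not remove the ambiguity, because the planned count at each timepoint depends on the chosen total.

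**4. Retention.** Planned retention under Sequence generation is 1 − 0.25 = 75%, inside the 60–76% amber band. Had the 77% figure been used to size the trial, the number to recruit would be 120/0.77 = 155.8, so 156 (39 blocks), one block fewer than stated.

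If true retention is 75%, the binomial probability of an observed green is:
- 120 randomised: 0.30 without rounding (93 or more retained), 0.38 if percentages are rounded (92 or more).
- 160 randomised: 0.26 without rounding (124 or more retained), 0.33 with rounding (123 or more).

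**The case against.** **The target is probably 120.** Primary feasibility outcomes asks whether the target sample size can be reached in the planned time. Sequence generation itself calls 120 the target sample size, and Recruitment pairs 120 with the 12-month period. This leans towards 120 but does not settle it: the progression criterion speaks of planned recruitment, and the only section that separates recruiting from the target plans to recruit 160.

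**The effect on the decision is limited.** A reader might infer that the choice of denominator decides whether a definitive trial goes ahead. The text after Table 4 does not support that. Progression can still be recommended with one red domain, subject to a remediation plan and a judgement that the barriers are remediable. Amber leads to amendments. The Discussion adds that the thresholds support decisions and are not rigid rules. This objection stands, although even a guideline needs a defined denominator.

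**The attrition gap is small.** The retention figure is approximate, 75% and 77% differ by two points, and a cautious inflation margin need not equal a success benchmark. This is fair, so the mismatch is secondary.

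**Two further criticisms are tempting but unsupported.** A reader might infer that some results, such as 92/120 = 76.7%, fall in no band. The bands are in whole percentages and conventional rounding closes the gaps. A reader might also object to a binomial interval for a count divided by a fixed target. The statistical methods section says only "Recruitment and retention will be summarized as proportions with 95% confidence intervals". It names no interval method, does not say that achieved over planned is the proportion meant, and no band uses an interval.

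**Conclusion.** The point holds as an internal inconsistency. The protocol gives two numbers to be randomised, 120 and 160, and leaves unnamed the denominator of a primary feasibility outcome. Enrolment of 102–111 is green on one and red on the other; 84–101 is amber or red; 112–135 is green or amber. These results rest only on the stated bands and the two stated totals.

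What is ambiguous is the colour rating. The overall progression verdict changes by rule only if the recruitment red is added to a red in another domain, since two or more reds mean not feasible without substantial redesign.

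Secondarily, retention exactly as planned under Sequence generation is rated amber. The probabilities of green given above assume true retention of 75% and independent participants, and they depend on whether percentages are rounded.

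**What to change.** Trial status says that recruitment has not begun, so all of this can be settled before any data exist:

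1. State one number to be randomised in the Abstract, Trial design, Sample size, Recruitment and Sequence generation, with the matching block count: 120 with 30 blocks (60 per arm), or 160 with 40 blocks (80 per arm).
2. Say explicitly whether 120 is the number randomised or the number retained.
3. Name the number randomised as the recruitment denominator in the progression text and Table 4, preferably with the cut-offs as counts (102 and 84, or 136 and 112).
4. Use one attrition assumption in Sequence generation, the retention section and the progression criteria.
5. Set the green retention cut-off so that retention at the planned rate is not amber, and give it as a count or with a rounding rule. With 120 randomised, 77% is 92.4 people; 92/120 = 76.7% is green only if rounded to a whole percent, and without rounding 93 are needed.

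The cost is wording. If 120 randomised is kept, about 90 to 92 participants, not 120, are expected with 12-month data. If 160 is kept, 40 more people must be enrolled in the same 12 months, about 13.3 a month (160/12) instead of 10 (120/12).

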#### Concealment mechanism

A study statistician will generate the randomization sequence in advance using permuted blocks. The sequence will be stored securely in the REDCap system and will not be accessible to study staff, except for the statistician. After the baseline interview, REDCap will assign the intervention based on the pre-generated sequence. A research assistant will facilitate this allocation process during the second recruitment interview.

#### Assignment of interventions: blinding

Due to the nature of the intervention, it is not feasible to blind participants, clinical staff delivering IPS, or the research team involved in its implementation. However, interviewers conducting baseline and follow-up quantitative assessments—covering employment, hospitalization, symptoms, functioning, and quality of life—will remain blinded to group assignment. Data analysts and statisticians will also be blinded during the analysis phase.

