IPS fidelity will be assessed using the 25-item IPS Fidelity Scale (IPS-25), a validated instrument with strong internal consistency and predictive validity [26]. Fidelity assessments will take place at approximately 6 and 12 months after program initiation. Experienced IPS reviewers will conduct in-person evaluations, including interviews with IPS staff, clinical team members, administrators, clients, and family members. Observations will cover vocational unit meetings, team discussions, and employer engagements. Reviewers will also examine selected participant records. Results will be used to monitor fidelity, highlight areas for adaptation, and guide ongoing quality improvement efforts.

The IPS Participation Measure is a brief form completed monthly by IPS Employment Specialists to track client engagement and services delivered (e.g., job search, career profiling, support provision) [21]. This tool captures information on employment status, IPS service participation, and reasons for non-participation [27]. IPS Employment Specialists will complete and submit the form monthly for each participant assigned to them. This measure was used with high completion rates in the Supported Employment Demonstration project and allows for the monitoring of IPS adaptations over time [28]. Tracking participation status and reasons for disengagement will support ongoing efforts to improve participant engagement in the IPS program.

Each month, IPS Employment Specialists will complete a service log documenting IPS activities performed during the previous week. This time-sampled approach has shown greater reliability than continuous measurement methods. Logs will capture time spent on various service categories, including direct versus indirect services, community-based versus in-office activities, collaboration with clinic-based mental health staff, job development (e.g., in-person employer meetings), and the delivery of job support. These data will allow for comparisons with current IPS program standards associated with high fidelity. Additionally, the information will help assess the extent to which IPS service delivery has been adapted through the Dynamic Adaptation Process.

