External interviewers with experience in clinical and social assessments will be recruited and trained prior to data collection. Both interviewers and IPS employment specialists will enter data using standardized online forms stored on a secure server. Centralized data entry will enable the study analyst to monitor data quality, identify missing or incorrect entries, and adjust data collection procedures as needed to ensure data integrity. All data collection activities will comply with the confidentiality protocols of the Center for Comprehensive Care in Long-Stay Mental Health.

Each quarter, the IPS Supervisor will receive a summary report based on the IPS employment specialists’ service logs. These summaries will support monitoring of IPS implementation and help identify areas requiring adjustment in collaboration with the IPS central team. The IPS Trainer will also receive the reports to assist the Supervisor in addressing challenges and reinforcing adherence to core IPS principles.

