## Data management

All trial data will be entered into a REDCap database [29] hosted by the research site. The system will track the completion of all study forms, including baseline, quarterly, and final assessments, as well as IPS participation data. Access will be password-protected, and users will only be able to access their assigned records. Any data entry errors will be corrected by authorized research staff, who will document the changes and the reasons for each correction. REDCap automatically maintains an audit trail of all edits and user activity. The Principal Investigator (PI) or designee will implement a data verification protocol and generate reports at the end of enrollment to monitor recruitment progress and assess covariate balance across study arms. The study statistician will review data completeness and IPS participation quarterly. At the end of the trial, data will be exported from REDCap as self-documenting SAS files for cleaning and analysis.

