### Monitoring

#### Data monitoring and reporting

The coordinating center, composed of the Principal Investigator, study coordinators, research staff, data analyst, and statistician, will hold monthly meetings to oversee daily trial operations. These include participant enrollment, data collection, intervention delivery, and compliance with regulatory requirements. An external steering committee, including experts in psychiatry, psychosocial rehabilitation, biostatistics, and mental health advocacy, will convene quarterly to review study progress and participant safety. This committee is independent of the sponsor and study team, and will provide guidance on trial continuation, protocol modifications, or early termination, based on safety indicators and study performance.

If the National Institute of Mental Health (NIMH) does not assign a Data and Safety Monitoring Board (DSMB), an independent board of local experts in Mexico will assume this role. No formal interim efficacy analyses are planned, as this is a feasibility study. However, the DSMB will review the final Data Safety Monitoring Plan, study protocol, protocol amendments, reportable adverse events, and annual progress reports.

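### The statistician who generates and holds the allocation sequence cannot be blinded at analysis as the protocol states, and blinding of the data analyst is doubtful

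*Protocol article*

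**What the plan says.** The protocol article makes one claim about the blinding of analysis staff and describes their duties in several other places.

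- **The claim** (Assignment of interventions: blinding): "Data analysts and statisticians will also be blinded during the analysis phase". It covers both roles and names no exception.
- **Sequence** (Concealment mechanism): "A study statistician will generate the randomization sequence in advance using permuted blocks". The stored sequence "will not be accessible to study staff, except for the statistician". No later removal of that access is described.
- **Quarterly review** (Data management): "The study statistician will review data completeness and IPS participation quarterly".
- **Source of participation data** (Plans for assessment and collection of outcomes): "IPS Employment Specialists will complete and submit the form monthly for each participant assigned to them".
- **Data checking** (same section): interviewers and IPS specialists both enter data through online forms, and "Centralized data entry will enable the study analyst to monitor data quality, identify missing or incorrect entries".
- **Staffing** (Data monitoring and reporting): the coordinating center is "composed of the Principal Investigator, study coordinators, research staff, data analyst, and statistician, will hold monthly meetings". Those meetings cover enrollment and intervention delivery, among other things.
- **Planned analyses** (Statistical methods for primary and secondary outcomes): the secondary analyses include "analyses based on level of exposure to the intervention".

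**The concern.** Blinding the people who analyse the data protects choices that are still open when the data arrive. Under Statistical methods, transformations are to be applied where needed, and pre-specified prognostic covariates are optional in adjusted models. Someone who knows the arms could, even unintentionally, settle such choices by what they do to the treatment contrast.

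The article offers analyst blinding as a property of the trial but gives the statistician duties that disclose allocation before the analysis phase opens. If nothing changes, the trial may report a blinded analysis that its own procedures contradict. The estimates concerned are the between-arm effect sizes with 95% confidence intervals for employment, financial well-being and health. Under Trial design, the pilot is also meant to supply estimates for planning a later regional trial.

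**Working it through.** There is no stated figure to reproduce and no formula applies. The check is to follow each role through the article and ask what it knows when analysis begins.

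**1. The statistician, through the sequence.** Concealment mechanism has a study statistician create the list and makes that role the one exception to the access bar on study staff. The unblinding section separately lets the principal investigator look up an assignment in exceptional circumstances, which does not alter the statistician's position. A person who has generated and held the list is unblinded, and limiting the claim to the analysis phase does not undo that knowledge. This step is sufficient for the statistician.

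**2. The statistician, through participation data.** Under Intervention description, only participants allocated to IPS are referred to the IPS team. The monthly participation form is completed by specialists for the participants assigned to them, so it exists only for the IPS arm. If the quarterly review is done by participant, the presence of a form identifies the arm. If it uses aggregate counts, it need not. The article does not say which, so this route is conditional.

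**3. Whether these are the same person.** Concealment mechanism refers to a study statistician and Data management to the study statistician. The coordinating center lists one. That they are the same person is a strong inference but is not stated.

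**4. The data analyst.** The analyst's checking covers what is entered centrally, and this includes entries by IPS specialists. Looking for missing entries on a form that only one arm has would show who is in that arm. Data management confines each user to assigned records, but nothing says that the analyst is kept from the IPS forms. The analyst also belongs to the group that meets monthly on intervention delivery. Blinding is therefore doubtful, but not disproved.

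**5. The exposure-level analysis.** Level of exposure to IPS is recorded in the IPS arm. Whoever runs this analysis learns the arms, so it cannot be done blind or come before the main comparative models are fixed.

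**6. What is exposed.**

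| Component | Depends on blinding of analysis staff? |
|---|---|
| Recruitment and retention proportions, fidelity scores, acceptability | No, descriptive |
| Progression criteria | No, none is a between-arm contrast |
| Blinding of outcome interviewers | No, a separate statement |
| Between-arm estimates for employment, finances and health | Yes, through optional transformations and covariates |

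**The case against.** The strongest reply is that the claim is limited to the analysis phase and that no section says who fits the final models. A second statistician, not described in the article, might do so. This stands in part: it rules out concluding that no blinded analysis will take place. It does not rescue the sentence, which covers statisticians without exception while the only statistician described holds the sequence.

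A second reply is that discretion is narrower than it may look. The covariates are to be pre-specified, and transformations follow from inspecting distributions rather than the arm contrast. This stands. What remains open is whether to adjust and whether to transform.

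A third reply is that masked codes, data exports and the timing of unblinding normally belong in a full protocol or analysis plan, which is not shown. This also stands, and their absence is not the point. The point is that the article's statement about blinding conflicts with the duties it assigns.

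Finally, this is a pilot with descriptive primary outcomes, and its Sample size section disclaims hypothesis testing. That limits the consequence but does not make the statement correct.

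**Conclusion.** As written, the blinding statement cannot be true of the statistician described under Concealment mechanism and Data management, and it is doubtful for the data analyst. Access to the sequence alone settles the first part. Extending it to everyone who will analyse the data assumes that the single statistician listed fills all the statistician roles. The second part assumes that the analyst sees the IPS forms individually, which the text suggests but does not state.

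The effect is modest and cannot be expressed as a number. It is an opportunity for bias in the exploratory between-arm estimates; nothing shows that any estimate would be altered.

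Three stronger readings go beyond the documents:

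- A reader might infer that the trial has no blinding at analysis. The article does not say who runs the final models, so this is not established.
- A reader might divide 24 months (12 of recruitment plus 12 of follow-up) by 3 and count about 8 unblinding reviews. The article does not say that the reviews are by participant, and the count adds nothing once the sequence is held.
- A reader might doubt the outcome-assessor blinding. It is a separate arrangement, and these sections do not touch it.

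**What to change.** Amend the blinding section and the related duties as follows.

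1. State that the statistician who holds the sequence and reviews IPS participation is unblinded, and neither chooses nor fits the comparative models.
2. Have those models fitted by an analyst who has no access to IPS-only forms during the trial and works from a dataset with masked arm codes until the models are locked.
3. Move checking of the IPS forms from the study analyst to the unblinded statistician or a coordinator. Without this step, naming the data analyst as the blinded modeller would leave the conflict in place. For the same reason, keep that analyst out of the parts of the monthly meetings that discuss individual IPS participants.
4. Run the exposure-level analysis only after unblinding.

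If existing staff cannot be separated in this way, delete the statement about data analysts and statisticians and report the analysis as unblinded. That is an acceptable outcome for exploratory comparisons in a pilot.

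The cost is protocol wording, a masked export and some reallocation of data checking. Whether it can be done without extra staff depends on who is available, since the article lists one analyst and one statistician. Trial status says recruitment has not begun, so the roles can be set before anyone sees allocations.
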